### **8.1.6.3 Analysis of Other Safety Endpoints**

**Adverse Events (TEAEs):** TEAEs during treatment are defined as adverse events that occur or worsen after the implantation of the investigational device. The number and incidence of the following TEAEs will be summarized by severity, System Organ Class (SOC), and Preferred Term (PT):

Adverse events

Device-related adverse events

Surgery-related adverse events

Adverse events leading to withdrawal

Serious adverse events

**Summary of Adverse Events:** Adverse events will be summarized according to SOC and PT, and the number of cases, frequency, and incidence will be calculated. The types of adverse events will be categorized by severity, SOC, and PT, and their

correlation with the test device will be assessed. The number of cases, frequency, and incidence will be calculated accordingly.

**Laboratory Test Indicators:** A cross-tabulation of laboratory test indicators, electrocardiogram (ECG), and physical examination results before and after treatment will be provided.

**Abnormal Cases:** Abnormal cases in laboratory indicators, ECG, physical examination, and their clinical interpretations will be listed.

**Vital Signs:** Descriptive statistics of vital signs after device implantation will be compared with baseline change values and actual measured values.

## **8.2 Calculation of sample size**

### **8.2.1 Total sample size**

According to literature reports and clinical experience, it is estimated that the success rate of valve repair with a prosthetic ring in the control group 6 months post-surgery is 95%, with a non-inferiority margin of -10%. Using a one-sided test,  $\alpha=0.025$ ,  $\beta=0.2$  (power 80%), the trial group and control group are to be matched at a ratio of 1:1. Using PASS 14.0 software, it is estimated that each group will require 75 cases. Considering the risk of dislodgement during the study process, it is planned to enroll 82 cases in each group, totaling 164 cases.

### **8.2.2 Number of clinical trial cases for each disease and the reasons for their determination**

According to the design requirements of this trial protocol, patients with tricuspid valve insufficiency were selected, and the number of samples was determined according to the statistical design to be 164.

### **8.2.3 Minimum and maximum number of subjects in each clinical trial institution and reasons for multicenter clinical trials**

This trial is expected to enroll 164 participants and will be conducted simultaneously at multiple clinical trial sites, implementing competitive enrollment. In principle, the number of participants enrolled at each center will be evenly distributed as much as possible to ensure adequate center representation. However, considering feasibility and enrollment progress, a competitive enrollment approach is adopted to maintain overall balance between groups.

## **8.3 Significance level and confidence level of clinical trials**

Non-inferiority testing is represented by the two-sided 95% confidence interval of the difference between groups. All statistical tests are conducted as two-sided tests; a P-value less than or equal to 0.05 will be considered statistically significant. With 164 patients selected, there is over 80% confidence that the efficacy of the treatment group is non-inferior to the control group.

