| 
Statistical Methods:
 
This trial plans to enroll 164 patients, who will be randomly assigned to either the experimental group or the control group in a 1:1 ratio, with 82 cases in each group.
 
The primary endpoint of this clinical trial is the success rate of valve repair at 6 months postoperatively, defined as no severe regurgitation and an increase in annular diameter of <math>\leq 15\%</math> based on echocardiographic evaluation. According to literature reports and clinical experience, the expected success rate of valve repair in the control group at 6 months postoperatively is 95%. Assuming that the investigational medical device can achieve comparable efficacy, the clinically accepted non-inferiority margin is set at -10%. With a one-sided significance level of 0.025 and a power of 80%, the sample size was estimated using PASS 14.0 software, indicating that 75 cases are required for each group. Considering potential dropouts during the study, the plan is to enroll 82 cases per group, totaling 164 cases.
 
The trial results will be determined based on the difference in the primary efficacy endpoint between the experimental group and the control group. If the lower limit of the 95% confidence interval for the difference in success rates between the experimental group and the control group is
 |                                                                                                                                                                                                                                                                                                                                                                                                                                                                                                                                                                                                                                                                                                                                                                                                                                                              |

greater than -10% (the predefined non-inferiority margin), the non-inferiority conclusion will be established. Otherwise, the non-inferiority conclusion will not be supported.

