#### **8.1.4 Analysis of the Primary Endpoint**

#### **8.1.5 Analysis of the Primary Efficacy Endpoints**

The success rate of valve repair with a prosthetic ring at 6 months post-surgery will be compared using the Newcombe method or Fisher's exact test to evaluate differences between groups. The Newcombe method will be used to calculate the two-sided 95% confidence interval (CI) for the rate difference between the experimental group and the control group. Non-inferiority will be assessed based on a non-inferiority boundary value of -10%. Both PPS and FAS analyses will be conducted.

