#### **8.4 Expected fall-off rate**

The expected fall rate is about 10%.

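### The power of over 80% stated for 164 patients does not hold for the planned Newcombe interval: it is about 74% with 82 per arm analysed and about 69% with 74

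*Protocol*

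**What the plan says.** The planning inputs are in the statistical methods paragraph of the synopsis and in section 8.2.1: control success of 95% at 6 months, a margin of -10%, one-sided 0.025, 80% power and 1:1 allocation. No separate rate is given for the test device. The synopsis says "Assuming that the investigational medical device can achieve comparable efficacy", which I read as 95% in both arms. Section 8.2.1 continues: "Using PASS 14.0 software, it is estimated that each group will require 75 cases". It then enrols 82 per arm, 164 in total, to allow for dropout. The test chosen in the software is not named. Section 8.4 expects about 10% dropout.

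The decision rule is fixed separately. Section 8.1.5 states: "The Newcombe method will be used to calculate the two-sided 95% confidence interval (CI) for the rate difference", to be compared with -10%. Section 8.5 repeats the Newcombe method as the criterion for a qualified result. Section 8.3 then attaches a power to the design: "With 164 patients selected, there is over 80% confidence that the efficacy of the treatment group is non-inferior to the control group".

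Section 8.1.5 calls for both the full analysis set (FAS) and the per-protocol set (PPS). Section 8.7 fills missing primary outcomes by last observation carried forward (LOCF).

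**The concern.** Power belongs to a sample size together with a decision rule. Here the sample size appears to come from one rule and the verdict from another. With success rates near 95% the two differ noticeably: the Newcombe interval has the lower limit further from zero than a Wald interval on the same data, so fewer outcomes pass.

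The 6-month result supports the registration submission. A sponsor, ethics committee or regulator reading section 8.3 would expect a chance below one in five of missing non-inferiority when the rings are equally good. If the true chance is nearer one in four, or three in ten, the trial is being run on a wrong figure.

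**Working it through.** **Inputs.** Success 95% in each arm, margin 0.10, one-sided 0.025 (z = 1.960), target power 80% (z = 0.8416), 82 enrolled per arm (synopsis and 8.2.1); loss of about 10% (8.4); Newcombe two-sided 95% interval (8.1.5, 8.5).

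**1. The plan's own figure.** The normal formula for two proportions gives

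n = (1.960 + 0.8416)² × 2 × 0.95 × 0.05 / 0.10² = 74.56, so 75 per arm.

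This reproduces the protocol exactly. Pooled and unpooled variances coincide when both rates are 95%, so it does not show which Z test was chosen. The same formula gives power of 80.2% at 75, 83.6% at 82 and 79.7% at 74.

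**2. The planned rule.** With Wilson 95% limits (l, u) for each arm, the Newcombe lower limit is

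L = (pT − pC) − √[(pT − lT)² + (uC − pC)²],

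and non-inferiority is declared if L > −0.10. Exact power is the sum, over all pairs of success counts, of the product of the two binomial probabilities at 0.95 wherever the rule is met.

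| Analysed per arm | Z formula | Wald interval, exact | Newcombe, exact |
|---|---|---|---|
| 74 | 79.7% | 82.1% | 69.1% |
| 75 | 80.2% | 81.7% | 71.8% |
| 82 | 83.6% | 84.2% | 74.0% |
| 92 | – | – | 78.9% |
| 93 | – | – | 80.2% |

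Simulation with 400,000 replicates gives 74.0% at 82 and 69.1% at 74. Letting 10% drop out at random in each arm, instead of fixing 74, gives 69.0%. Newcombe power first reaches 80% at 93 per arm and does not fall below it from there.

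**3. One outcome, for illustration.** Take 76/82 (92.68%) on test and 78/82 (95.12%) on control, a difference of −2.44 points.

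- Wald: −0.0244 − 1.960 × √(0.9268 × 0.0732/82 + 0.9512 × 0.0488/82) = −0.0975, which passes.
- Newcombe: Wilson lower limit 0.8494 on test and upper limit 0.9809 on control, so −0.0244 − √(0.0774² + 0.0296²) = −0.107, which fails.

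**4. Dropout.** 82 × 0.9 = 73.8, below the 75 that the plan requires. 75/0.9 = 83.3, so 84. The loss that 82 can absorb is 1 − 75/82 = 8.5%.

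**5. Sensitivity to the 95%.** With equal true rates and 82 per arm, Newcombe power is 79.9% at 96.0% and 80.2% at 96.05%. With 74 per arm it is 80.3% at 96.5%. If control stays at 95% and 82 per arm are analysed, power is 61.4% with test at 94% and 85.1% with test at 96%.

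**6. Error rate at the margin (test 85%, control 95%).** Exact one-sided error is 2.35% (82 per arm) and 2.1% (74) for Newcombe, against 3.3% and 3.75% for Wald.

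**The case against.** The best defence is that the sponsor's sum is right. For a simple Z test 75 per arm is correct, and 82 analysed per arm gives about 84%. That stands, and a reader who inferred a slip in the calculation would go too far. The fault is a mismatch between the planning test and the decision rule. Nor do the documents prove that a Wald test was used, because the software's test is not named. What can be said is that the figure matches a simple Z calculation and is not the power of the Newcombe rule.

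A reader might also infer that the trial simply has 69% power. That figure is conditional. LOCF can keep a dropout with an earlier value in the FAS, and 74% then applies if all 82 per arm are implanted and carry an outcome. The 69% belongs to the PPS or to complete cases, with about 74 per arm. Neither reaches 80%.

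The dropout shortfall is small. The plan says about 10%, 82 covers 8.5%, and on the Z formula 74 instead of 75 costs only half a point (79.7% against 80.2%). Confidence for power is probably a translation slip, since the synopsis and 8.2.1 speak of power. Both are worth correcting alongside the main point, but neither carries it.

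Finally, the 95% is an assumption, and true rates may be higher. But section 8.3 gives its figure without that condition, and the protocol plans on 95%.

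**Conclusion.** The statement in 8.3 is wrong for the planned analysis. Under the protocol's assumptions (95% in both arms, margin -10%, two-sided 95% Newcombe interval), power is about 74% with 82 per arm analysed and about 69% with 74. The chance of missing non-inferiority between truly equal devices is thus 26% or 31%, against the planned 20%. The result rests on reading comparable efficacy as a true difference of zero and on the Newcombe interval without continuity correction.

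It would be tempting to infer that the primary conclusion is unsafe. The documents do not support that. The margin and the decision rule are unaffected, and the Newcombe rule keeps its one-sided error below 2.5% in the case checked. The added risk is of a false negative result, not of a false claim of non-inferiority.

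**What to change.** In the synopsis, 8.2.1 and 8.3:

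- State power for the Newcombe rule at 95% in both arms: about 74% with 82 analysed per arm (FAS with LOCF and no outcome missing) and about 69% with 74 per arm (PPS or complete cases after 10% loss).
- State that 80% holds, with equal true rates, only if success is just above 96.0% at 82 per arm, or about 96.5% at 74.
- State that 82 per arm covers about 8.5% loss, not the 10% in 8.4.
- Name the test behind the 75, and write power instead of confidence.

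Keep the Newcombe interval. Changing to Wald would bring the stated power back, but its one-sided error of about 3.3% to 3.8% exceeds the 2.5% that the plan sets.

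The cost is a change of wording and a less favourable stated power. No extra patients are needed to make the statement true. If the sponsor wants a real 80% at 95%, the requirement is 93 evaluable per arm; with 10% loss, 93/0.9 = 103.3, so 104 per arm and 208 in total.

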#### **8.4 Expected fall-off rate**

The expected fall rate is about 10%.

#### **8.5 Criteria for qualified/unqualified clinical trial results**

Determining whether the experimental results are qualified from a statistical perspective is equivalent to verifying the initial hypothesis test. For this study, it is necessary to meet the non-inferiority test for the primary efficacy endpoint, which involves calculating the rate difference between the treatment group and the control group using the Newcombe method for the success rate of valve repair with prosthetic rings at 6 months post-surgery, and assessing whether the efficacy of the treatment group is not inferior to that of the control group based on a non-inferiority margin of -10%.

#### **8.6 Criteria and reasons for terminating the trial on statistical grounds**

A non-inferiority design is adopted, with the non-inferiority margin  $\delta$  set at -10%.

H0 (null hypothesis):  $P1 - P2 \leq \delta$

H1 (alternative hypothesis):  $P1 - P2 > \delta$

Where P1 is the success rate of valve repair with a prosthetic ring at 6 months post-surgery in the experimental group, and P2 is the success rate of valve repair with a prosthetic ring at 6 months post-surgery in the control group.  $\delta$  represents the non-inferiority margin.

#### **8.7 Statistical methods for all data, including processing of missing, unused or erroneous data (including dropout and withdrawal) and unreasonable data**

When the main indicators are missing, the last observation value carry-over method (LOCF) is used to fill in the data. Other indicators are analyzed using the actual collected data.

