#### **7.1.2.3 Rationale for Selecting the Primary Endpoint:**

The primary goal of the Annuloplasty Ring is to repair and reshape the diseased valve annulus, ensuring proper leaflet coaptation (the area where the valve leaflets meet). For patients with tricuspid regurgitation (leaky valve), the main evaluation metric after annulus repair is the success rate of the Annuloplasty Ring at 6 months post-surgery. Definition of Repair Success: No Severe Regurgitation: Postoperative echocardiography (heart ultrasound) must show no severe valve leakage. Annular Dilation  $\leq 15\%$ : The increase in the annular size (measured by echocardiography) must be 15% or less compared to preoperative measurements.

Secondary Efficacy Endpoints

The secondary endpoints for evaluating effectiveness include the following assessments at discharge or 30 days post-surgery (whichever comes first), and at 3 months, 6 months, and 12 months post-surgery:

Degree of Valve Regurgitation: Assessed by echocardiography (heart ultrasound) to measure the severity of valve leakage.

Echocardiographic Parameters: Changes in the following measurements will be evaluated:

Size of the right atrium and right ventricle.

Annular dimensions (diameter).

Width of the narrowest part of the regurgitant jet.

Area of reverse blood flow.

NYHA Functional Class: A measure of heart failure symptoms and functional capacity, classified as Class I (no symptoms) to Class IV (severe symptoms).

Freedom from Reoperation: The rate of patients who do not require repeat surgery for tricuspid regurgitation.

Device Performance Evaluation:

Suture Needle Ease of Use: How smoothly the needle passes through the Annuloplasty Ring during implantation.

Holder Device Usability: How user-friendly the ring holder is during the procedure.

Surgical Technical Success:

Defined as the following criteria being met before leaving the operating room:

No intraoperative death.

Successful implantation of the Annuloplasty Ring.

Successful removal of the ring holder.

No need for emergency surgery or additional interventions related to the investigational device.

Safety Endpoints:

Safety will be assessed at discharge or 30 days post-surgery (whichever comes first), and at 3 months, 6 months, and 12 months post-surgery. The following will be evaluated:

Serious Adverse Events (SAEs): Including:

Cardiovascular-related deaths linked to the device.

Major bleeding linked to the device.

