#### **7.1.5.3.4 Regulatory Authority Decision**

The trial will be stopped if a regulatory agency withdraws approval or orders termination. In any of these cases, the sponsor must immediately inform all participating hospitals, investigators, and ethics committees. For participants who have already received the trial treatment, the sponsor will continue to follow legal requirements and uphold responsibilities outlined in the informed consent form. Participants have the right to withdraw from the trial at any time for any reason. Researchers also have the right to withdraw participants from the trial in the event of complications, adverse events, treatment failure under standard therapy, violation of the protocol, cure, or other reasons.

Excessive participant withdrawals can compromise the reliability of the trial results. Therefore, every effort should be made to avoid unnecessary withdrawals. If a participant decides to withdraw, the investigator should make every effort to persuade them to stay and document the reasons for withdrawal in detail. Documenting Withdrawal Reasons. If a participant withdraws due to an adverse event or abnormal lab results, the investigator must record the event or abnormality in the electronic Case Report Form (eCRF). The investigator should also attempt to contact the participant (or their family) via phone, in-person visits, or other means to gather detailed information about the withdrawal. Specific Reasons for Discontinuation by the Investigator.

The investigator may also decide to discontinue a participant's involvement in the trial under the following circumstances:

**Pregnancy:** If the participant becomes pregnant during the trial.

**Protocol Violations:** If the participant fails to follow the trial procedures or requirements.

**Complications or Adverse Events (AEs):** If the participant experiences serious side

effects, abnormal lab results, or other medical conditions that could worsen by continuing the trial.

**Non-Compliance:** If the participant fails to adhere to the trial treatment or procedures.

**Adverse Events or Medical Conditions:** If continuing the trial poses a risk to the participant's health.

**Disease Progression:** If the participant's condition worsens, requiring discontinuation of the trial treatment.

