### **7.1.6 Efficacy Evaluation Methods**

#### **7.1.6.1 Description of Efficacy Parameters**

Primary efficacy endpoint: The success rate of valve annuloplasty repair at 6 months postoperatively, defined as no severe regurgitation and an increase in diameter  $\leq 15\%$  (based on a comprehensive assessment of regurgitation severity and diameter increase).

Other efficacy endpoints:

**7.1.6.1.1** At discharge or 30 days postoperatively (whichever comes first), 3 months, 6 months, and 12 months:

- Degree of valve regurgitation assessed by echocardiography (evaluated according to the tricuspid regurgitation assessment index table).
- Changes in echocardiographic parameters (right atrial and ventricular size, diameter, width of the narrowest regurgitation jet, and reverse flow area).
- NYHA functional class.
- Freedom from reoperation due to tricuspid valve insufficiency.

**7.1.6.1.2** Evaluation of the trial device's performance, including needle insertion smoothness and user-friendliness of the ring holder.

**7.1.6.1.3** Technical success rate of the surgery (before leaving the operating room), defined as no intraoperative death, successful implantation of the annuloplasty ring, successful removal of the ring holder, and no emergency surgery or secondary

intervention related to the trial device.

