#### 7.1.6.2.2 Diameter measurement method:

Maintain the postoperative annular shape, measure the average of three diastolic annular diameters using TTE or TEE.

- Annular long diameter (A2): Measured in the standard apical four-chamber view, representing the left-right diameter of the tricuspid annulus.
- Annular short diameter (B2): Measured in the standard right ventricular inflow view, representing the superior-inferior diameter of the tricuspid annulus.

[figure not shown]

An increase in diameter is defined as the difference between the 180-day postoperative annular diameter and the 3-month follow-up diameter, divided by the 3-month follow-up diameter. An increase of more than 15% in both long and short diameters is considered significant.

**7.1.6.2.3 Echocardiographic parameters:** Measure right atrial and ventricular size, width of the narrowest regurgitation jet, and reverse flow area.

TTE evaluations will be conducted at discharge or 30 days ( $\pm 7$  days), 3 months ( $\pm 15$  days), 6 months ( $\pm 30$  days), and 12 months ( $\pm 30$  days) postoperatively.

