### **7.1.8 Trial Endpoints**

Primary endpoint: The success rate of valve annuloplasty repair at 6 months postoperatively, defined as no severe regurgitation and an increase in diameter  $\leq 15\%$  (based on a comprehensive assessment of regurgitation severity and diameter increase).

Secondary endpoints:

**7.1.8.1** At discharge or 30 days postoperatively (whichever comes first), 3 months, 6 months, and 12 months:

**7.1.8.1.1** Degree of valve regurgitation assessed by echocardiography (evaluated according to the tricuspid regurgitation assessment index table).

**7.1.8.1.2** Changes in echocardiographic parameters (right atrial and ventricular size, diameter, width of the narrowest regurgitation jet, and reverse flow area).

**7.1.8.1.3** NYHA functional class.

**7.1.8.1.4** Freedom from reoperation due to tricuspid valve insufficiency.

**7.1.8.2** Evaluation of the trial device's performance, including needle insertion smoothness and user-friendliness of the ring holder.

**7.1.8.3** Technical success rate of the surgery (before leaving the operating room), defined as no intraoperative death, successful implantation of the annuloplasty ring, successful removal of the ring holder, and no emergency surgery or secondary intervention related to the trial device.

**7.1.8.4** At discharge or 30 days postoperatively (whichever comes first), 3 months, 6 months, and 12 months:

**7.1.8.4.1** Incidence of serious adverse events, including cardiovascular death, major bleeding, severe damage to cardiac or other body structures, infective endocarditis, and thromboembolic events related to the trial device.

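### LOCF on an echo-only primary endpoint can score deaths and outcome-related withdrawals as repair successes in the FAS, while the PPS drops them, so neither set counts them as failures

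*Protocol*

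**What the plan says.** - **Missing data (Protocol 8.7).** "When the main indicators are missing, the last observation value carry-over method (LOCF) is used to fill in the data". The section heading covers dropout and withdrawal. The section names no other method for the primary endpoint and no sensitivity analysis.
- **Primary endpoint (7.1.6.1, repeated in 7.1.8 and the synopsis).** "The success rate of valve annuloplasty repair at 6 months postoperatively, defined as no severe regurgitation and an increase in diameter" of at most 15%. Both components are echo findings. "Freedom from reoperation due to tricuspid valve insufficiency" is a separate secondary endpoint (7.1.8), as is all-cause mortality. Nothing in the protocol counts either event as a primary failure.
- **Diameter reference.** Section 7.1.6.2.2: "An increase in diameter is defined as the difference between the 180-day postoperative annular diameter and the 3-month follow-up diameter". That difference is then expressed as a proportion of the 3-month value. Section 7.1.2.3 instead says the increase "must be 15% or less compared to preoperative measurements".
- **Withdrawal (7.1.5.3.4).** "Researchers also have the right to withdraw participants from the trial in the event of complications, adverse events, treatment failure under standard therapy".
- **Analysis sets (8.9, 8.1.5).** The FAS is all randomized and implanted patients. The PPS further requires that the primary endpoint was measured. The primary analysis is run on both.

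**The concern.** A patient who dies at month 4, or is withdrawn because the repair is failing, has no 6-month echo. If the last echo was not severe, the rule in 8.7 fills in a favourable result for a patient whose treatment did not succeed. Withdrawal for complications or treatment failure is expressly allowed, so missingness can depend on outcome. About 10% dropout is expected (8.4).

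The usual reassurance in a non-inferiority trial is agreement between FAS and PPS. Here the FAS can score such a patient as a success and the PPS leaves the patient out, so agreement says nothing about these events. The primary comparison is the sole criterion for a positive trial (8.5).

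**Working it through.** **Step 1. The plan's own figure.** Inputs from 8.2.1: 95% success in control, margin 10 points, one-sided alpha 0.025, power 80%; equal success in the test arm as assumed in the synopsis.

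n = (1.960 + 0.842)² × 2 × 0.95 × 0.05 / 0.10² = 74.6, so 75 per group. This matches the protocol. Enrolment is 82 per group. The design inputs are not in dispute.

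**Step 2. What the rule does, case by case.** D3 is the 3-month diameter.

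| Situation | Result as written |
|---|---|
| Death or withdrawal after a non-severe 3-month echo | FAS: regurgitation component passes. Diameter increase (D3 − D3)/D3 = 0% under 7.1.6.2.2, so it passes automatically. PPS: excluded |
| Severe regurgitation on the last echo | FAS: carried forward as failure |
| Only a discharge/30-day echo | The increase in 7.1.6.2.2 has no 3-month denominator and cannot be computed |
| No postoperative echo | No postoperative value to carry; rule undefined |
| Reoperated, 6-month echo done and good | Not missing. Can score as success through the endpoint definition, not LOCF |

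Under the preoperative reference of 7.1.2.3 the carried diameter is compared with a different value, so the pass is no longer automatic.

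**Step 3. Size, by assumption.** Let f be the share of true failures, the same in both arms, that are missing at 6 months and carried forward as success. With 82 per arm at the margin (true 85% versus 95%), apparent success is 1 − 0.15(1 − f) versus 1 − 0.05(1 − f), and the apparent difference is −10(1 − f) points. The false-claim rate is the exact binomial probability that the lower limit of the two-sided 95% Newcombe interval exceeds −10%.

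| f | Apparent success, test vs control | Difference (points) | False non-inferiority rate |
|---|---|---|---|
| 0 | 85.0% vs 95.0% | −10 | 2.35% |
| 10% | 86.5% vs 95.5% | −9 | 3.7% |
| 20% | 88.0% vs 96.0% | −8 | 5.9% |
| 30% | 89.5% vs 96.5% | −7 | 9.4% |
| 50% | 92.5% vs 97.5% | −5 | 23.0% |

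**Step 4. A single data set.** Suppose 3 echo failures per arm, plus 4 test and 2 control deaths or reoperations, each after a good early echo and with no 6-month echo. The Newcombe lower limit is d − √[(p₁ − l₁)² + (u₂ − p₂)²], where l₁ is the lower Wilson limit in the test arm and u₂ the upper Wilson limit in control.

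- LOCF: 79/82 vs 79/82, d = 0. Lower limit = −√[(0.9634 − 0.8979)² + (0.9875 − 0.9634)²] = −7.0%. Non-inferiority is claimed.
- Events counted as failures: 75/82 vs 77/82, d = −2.4%. Lower limit = −0.0244 − √[(0.9146 − 0.8341)² + (0.9737 − 0.9390)²] = −11.2%. Non-inferiority is not shown.

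**The case against.** **Early failures become successes.** A reader might infer this. It is too broad: severe regurgitation already seen on the last echo is carried forward as failure. Only an event after a non-severe last echo is masked. Section 7.1.5.3.4 permits withdrawal but does not require it, and 7.2.5 schedules a 6-month echo for everyone, so reoperated patients need not be missing.

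**The bias always favours the test ring.** The documents do not support this. Direction depends on which arm has more masked failures; an excess in control would penalise the test ring.

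**The false-claim rate could reach 92%.** It can be constructed: assume 98% echo success in event-free patients and events in 3% of controls versus 13% of test patients. True success is then 95.1% versus 85.3%, and the chance of claiming non-inferiority is 2.6% if events are failures and 92% if every one is masked. The imbalance appears nowhere in the documents, and complete masking is the extreme. With 3% versus 8% the figures are 20% and 92%, but the true difference (90.2% − 95.1% = −4.9 points) lies inside the margin, so that claim would be correct. The control-ring series in 4.2 (4 deaths in 75, or 5.3%; the printed 53% does not match) averaged 16 months of follow-up, so it does not give a 6-month event rate here.

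**The SAP may deal with it.** Section 8.1.1 defers detailed methods to a separate SAP, and mortality and reoperation are compared between arms anyway. It is true that the protocol is only silent on how death is scored, and that a composite is partly a choice of estimand. But LOCF is stated in the protocol, and combined with the endpoint as written it gives the result in step 2.

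**Conclusion.** The concern stands in a conditional form. As written, a death or outcome-related withdrawal after a non-severe 3-month echo is a success in the FAS and absent from the PPS. The defect is in a stated rule governing the sole success criterion, so it should be corrected before analysis.

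The size cannot be read from the documents. If the test ring is truly at the margin and failures are masked in equal proportion in both arms, masking 10% already takes the error rate above the planned 2.5% (to 3.7%), and masking 50% takes it to 23.0%. In the worked example, six masked patients decide the conclusion.

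**What to change.** 1. In 7.1.6.1 and 8.7, count death, tricuspid reoperation, ring explant or conversion to replacement, and withdrawal for treatment failure before the 6-month echo as primary failures. This also settles the reoperated patient who has a good 6-month echo.
2. For other missing 6-month echoes, replace LOCF with multiple imputation within arm, supported by a tipping-point analysis.
3. Keep missing = failure as a sensitivity analysis only. It is not neutral: with 10% missing at random, success at the margin becomes 0.9 × 85% = 76.5% versus 0.9 × 95% = 85.5%, the false-claim rate is 3.75%, and exact power at equal 95% falls from 74% to 44%.
4. Keep collecting the 6-month outcome after withdrawal unless consent is withdrawn. This concerns data collection only.
5. Reconcile the diameter reference in 7.1.2.3 with that in 7.1.6.2.2.

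**Cost.** The changes are wording and some programming, but the success rate may be a few points lower. If a further 5% per arm fail on top of 95% echo success, the rate is 0.95 × 0.95 = 90.25% in each arm, and exact Newcombe power at 82 per arm falls from 74% to 55%. The 95% assumption in 8.2.1 should therefore be restated for the redefined endpoint and the sample size checked against it.
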